**Methods and analysis:**

This matched quasi-experimental study design using non-randomised intervention and control clusters was designed to assess the effectiveness of an urban simplified sewerage intervention in the low-income communities of Salvador, Brazil. The intervention consists of household-level piped sewerage connections and community engagement and public involvement activities. A cohort of 1400 adult participants will be recruited and grouped into eight clusters consisting of four matched intervention-control pairs with approximately 175 individuals in each cluster in baseline. The primary outcome is the seroincidence of *Leptospira* infection assessed through five serological measurements: one preintervention (baseline) and four postintervention. As a secondary outcome, we will assess *Leptospira* load in soil, before and after the intervention. We will also assess *Leptospira* exposures before and after the intervention, through transmission modelling, accounting for residents' movement, contact with flooding, contaminated soil and water, and rat infestation, to examine whether and how routes of exposure for *Leptospira* change following the introduction of sanitation.

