## Methods and analysis

### Overview of study design

This is an intervention trial with a cluster non-randomised controlled trial, with eight clusters (four intervention and four control), including longitudinal serological follow-up of 1400 adults’ residents from disadvantaged urban communities at high risk for leptospirosis transmission in Salvador, Bahia, Brazil. The primary outcome will be *Leptospira* infection. Each pair of intervention and control clusters will be allocated in distinct hydrological sub-basins with distances from 1000 to 1500 m apart. Clusters will be matched on socioeconomic status (SES), topographic or hydrological characteristics, population density, and *Leptospira* seroprevalence. The cluster selection will also consider exposure to the pathogen by selecting houses that are located to similar distances to new sewerage system and control open sewers. The intervention aims at a combination of sanitation (simplified sewerage intervention) and community engagement activities.

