#### Secondary outcomes

##### Environmental exposure secondary outcomes

Secondary outcomes for environmental effects will include microbiological assays to assess soil contamination with pathogenic *Leptospira*. The presence and concentration of pathogenic *Leptospira* will be evaluated in the eight clusters. Bases on prevalence the contamination soil with *Leptospira* in studies previous and packing density of 0.4 with minimum distances between collection points, a total of 68 soil samples and 15 water sewage samples will be collected in each cluster and transported refrigerated to the laboratory within 6 hours for processing. Sampling will take place in duplicate, with intervals of 7–9 days between them. After processing, soil and sewage samples will be stored at −80°C until molecular assays can be performed. The presence and concentration of pathogenic *Leptospira* will be evaluated using a qPCR assay (quantitative PCR), targeting the *lipL32* gene. Samples will be considered positive when the two qPCR replicates show amplification before a Cq of 40.^7^ Environmental variables for rainfall, temperature, landscape (remote sensing using drones), flooding and hydrological features will also be collected during rainy seasons before and at least 3 months immediately after the sewerage intervention.

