### Statistical analysis

Descriptive statistics will be employed to report the demographic, social, economic or environmental characteristics between the study clusters (intervention and control clusters). For the primary outcome, we will apply quasi-Poisson regression to estimate the incidence rate ratio of *Leptospira* infection. We will also evaluate the effect of the intervention on *Leptospira* infection risk using mixed-effects logistic regression models to account for clustering of the observations within study units and across repeated measures for individuals. We will model the overall effect of the intervention on infection risk while controlling for baseline sewerage and flooding exposure and potential confounding variables, such as age, sex, indicators of the socioeconomic level, and rainfall intensity during an annual period, which are presumably unrelated to the intervention (figure 1).

For the secondary outcome, we will conduct environmental analyses of *Leptospira* load between intervention and control clusters to compare environmental risk. To do this, we will model two leptospiral load outcomes, prevalence (binomial) and concentration (log-transformed), using generalised linear models with random effects to account for clustering within study units. The association between environmental contamination and hypothesised predictors of risk (rat abundance, human movement and ecological data) will also be explored in the model (figure 1).

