### Limitations and bias

The allocation is non-randomised with selection based on intervention criteria determined by the implementer so the risk of residual confounding cannot be excluded. The choice of the control group is also dependent on the implementer’s information about the non-intervention in the area in the short term (5-year period). To limit the potential for bias arising from our non-randomised design, we will select control group with as similar as possible socioeconomic and environmental characteristics to those of their matched intervention clusters.

We will perform the impact calculation through the double differentiation of the averages of the results found between the intervention and control clusters before and after the sewerage intervention. The mitigation of bias will be carried out through the control of fixed effects of time and location between different intervention and control clusters over the years of evaluation.

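### For soil load, the named model effects leave out cluster-by-period variation; if the double difference is tested at sample level with only those effects, its false-positive rate exceeds 5%

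*Protocol article*

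**What the plan says.** The abstract makes soil load a before/after outcome: "As a secondary outcome, we will assess *Leptospira* load in soil, before and after the intervention". The design has "eight clusters consisting of four matched intervention-control pairs". Under Environmental exposure secondary outcomes, "a total of 68 soil samples and 15 water sewage samples will be collected in each cluster", and sampling is done in duplicate 7–9 days apart.

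Statistical analysis describes the soil comparison as one between intervention and control clusters. Prevalence (binomial) and log-transformed concentration are modelled "using generalised linear models with random effects to account for clustering within study units". Rat abundance, human movement and ecological data are to be explored as predictors.

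Limitations and bias adds how impact is calculated: "double differentiation of the averages of the results found between the intervention and control clusters before and after the sewerage intervention". Bias is to be reduced by "control of fixed effects of time and location between different intervention and control clusters over the years of evaluation".

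The effects named across the two sections are therefore study unit, location and time. Neither section names a cluster-by-period effect, a cluster-level test or small-sample degrees of freedom. In the same Statistical analysis section, the infection model lists two levels of dependence (study unit, and repeated measures on a person); the soil model lists one.

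**The concern.** A term that describes how clusters differ on average does not protect a comparison of how they change. In a before/after double difference, a cluster effect that is the same in both rounds subtracts out. What remains is the intervention effect, sampling noise, and whatever each cluster did on its own between rounds. If the model has no term for the last of these, it treats ordinary local change as evidence about the intervention.

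The article gives reasons to expect such change. The paired clusters lie in distinct hydrological sub-basins, transmission is tied to rainfall and flooding, and the works run over 2022 and 2023 on the company's own schedule.

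Reduced soil load is a secondary outcome and the third of the hypothesised effects. With error bars that are too narrow, the trial could report that sewerage lowered or raised soil contamination when four clusters per arm merely fluctuated differently between rounds.

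**Working it through.** **Inputs from the protocol article.** Eight clusters, four per arm, in four matched pairs (Abstract; Overview of study design). 68 soil samples per cluster, taken in duplicate, so m = 68 per cluster per round, or 2 × 68 = 136 if every duplicate is analysed as an independent sample (Environmental exposure secondary outcomes). The article states no error rate, prevalence, standard deviation or power for soil, so there is no figure of its own to reproduce.

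**Assumptions, not in the article.** Two-sided 5% test; no intervention effect; cluster-by-period correlation ρ between 0.001 and 0.03. Here ρ is the share of a sample's variance, after removing the constant cluster effect, that is common to all samples from the same cluster and round. The only clustering figure stated is 0.03, a between-cluster value for human infection. It is a different quantity and merely marks the top of the assumed range.

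**Step 1: what cancels.** Write the mean of cluster j in round t as

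ȳ_jt = μ + c_j + p_t + δ·arm_j·post_t + g_jt + ē_jt,

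where c_j is the cluster effect, g_jt the cluster-by-period effect and ē_jt the sampling noise. The change in cluster j is

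D_j = (p_1 − p_0) + δ·arm_j + (g_j1 − g_j0) + (ē_j1 − ē_j0).

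c_j is gone, whether it was fitted as random or fixed. The variance of D_j, scaled to unit sample variance, is 2[ρ + (1 − ρ)/m]. A sample-level model without g uses about 2/m. The ratio is

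DE = 1 + (m − 1)ρ.

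**Step 2: false-positive rate.** Rejection = 2·Φ(−1.96/√DE).

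| ρ (assumed) | DE, m = 68 | Rejection, m = 68 | DE, m = 136 | Rejection, m = 136 |
|---|---|---|---|---|
| 0 | 1.000 | 5.0% | 1.000 | 5.0% |
| 0.001 | 1.067 | 5.8% | 1.135 | 6.6% |
| 0.005 | 1.335 | 9.0% | 1.675 | 13.0% |
| 0.01 | 1.670 | 12.9% | 2.350 | 20.1% |
| 0.03 | 3.010 | 25.9% | 5.050 | 38.3% |

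Example: m = 68, ρ = 0.01 gives DE = 1 + 67 × 0.01 = 1.67, √DE = 1.292, 1.96/1.292 = 1.517, and a two-sided rejection rate of 12.9%.

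The rate reaches 10% when ρ = ((1.96/1.645)² − 1)/(m − 1), which is 0.0063 for m = 68 and 0.0031 for m = 136.

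**Step 3: simulation with no effect.** A linear mixed model with a random cluster intercept only, m = 68, 300 runs per setting, rejected 5% of the time at ρ = 0, 16% at 0.01 and 24% at 0.03. Some of these fits gave convergence or boundary warnings, but the rates agree with the formula within simulation error. A binomial model with cluster and period fixed effects plus arm-by-period (prevalence 0.15 or 0.30 assumed, 1500 runs per setting) gave about 13% at 0.01 and 26% at 0.03 for m = 68, and about 20% and 36–38% for m = 136.

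**Step 4: cluster-level tests in simulation.** A t-test on the eight cluster changes (6 df) rejected 3.0–6.0% of the time, and a paired t-test on the four within-pair differences in change (3 df) 3.7–6.0%. The spread of the D_j already contains g, which is why both stay near nominal.

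**The case against.** The strongest reply is that the article does not state the faulty model. It speaks of random effects without giving their structure, and a cluster-by-period random effect would fit that sentence. It speaks of differencing averages; done on cluster-period averages with cluster-level degrees of freedom, that is a sound analysis. The double difference and the time and location effects come from Limitations and bias, which does not mention soil. If the soil model instead compares arms in the post-intervention round alone, the cluster random effect does not cancel and is the right error term. Random-effect structure is often left to a fuller plan. Local drivers are also measured, the clusters are matched on hydrology, and covariates will be explored.

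Much of this stands. A reader might infer that the plan uses only time-constant cluster effects, or that false positives will be several times 5%. The article supports neither as fact: the first is a reading of what is named, and the second depends on a correlation that is not given.

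What remains is that the article is not silent. It names a model as accounting for clustering and a before/after contrast as the measure of impact, and the effects named do not protect that contrast. Where the authors meant two levels of dependence, for infection, they listed two. Exploring covariates is no reliable repair: rat infestation is itself something the intervention is hypothesised to reduce, so adjusting for it would change the effect being estimated.

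**Conclusion.** The point holds conditionally. The natural reading of the named effects omits cluster-by-period variation. If the soil double difference is tested at sample level on that basis, the false-positive rate at a nominal 5% is about 6% to 26% with 68 samples per cluster per round, for assumed correlations of 0.001 to 0.03. With 136 it is about 7% to 38%; this is an upper bound, because duplicates taken 7–9 days apart are unlikely to be fully independent. At 0.001 or less the problem is small.

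The text permits both a sound analysis and an unsound one, and the two could give quite different p-values from the same data. That choice should be settled before the post-intervention samples are analysed. The calculation was made for soil load and is not extended here to other outcomes.

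**What to change.** In Statistical analysis and in Limitations and bias, state for soil load that the double difference is tested at cluster level, and name one method in advance:

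- compute each cluster's before/after change (log odds of positivity; mean log concentration) and compare the eight changes between arms on 6 df;
- if the matching is kept, test the four within-pair differences in change on 3 df; or
- keep the sample-level model, add a cluster-by-period random effect, and test the arm-by-period term with small-sample, cluster-level degrees of freedom.

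These are not equivalent: they differ in assumptions, degrees of freedom and power. Take the reported confidence interval from the method chosen, and say how the duplicates enter the analysis.

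The cost is some wording and a few lines of code, with no new data. The downside is wider confidence intervals and lower nominal power for the soil comparison, which is what four clusters per arm can support.

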### Research aims and hypotheses

We hypothesise that the combination of a simplified sewerage infrastructure and community engagement activities will reduce the risk of *Leptospira* infection among disadvantaged urban communities in Salvador, Brazil. We further hypothesise that this approach will be effective in reducing: (1) frequency of human contact with open sewerage contaminated with pathogenic *Leptospira*; (2) rat infestation and (3) *Leptospira* load in the soil around the simplified sewerage. We aim to evaluate the efficacy of a sewerage intervention on reducing *Leptospira* infection and other health outcomes related to sanitation in disadvantaged urban communities in Brazil. Our specific objectives are to: (1) to evaluate prospectively the effectiveness of a simplified sewerage intervention in reducing the risk of *Leptospira* infection; (2) to determine the mechanisms by which the simplified sewerage reduce direct human contact with environmental pathogen load in urban slums. Figure 1 provides further details on our hypotheses concerning the effects of the sanitation intervention on the transmission mechanisms of urban leptospirosis. We conceptualise this protocol as focusing on the sanitation intervention to decrease leptospirosis; however, this study protocol generates rich opportunities to evaluate other health outcomes. Therefore, we additionally aim to investigate the effects of the sewerage intervention on childhood exposure to a range of enteropathogens, and long-term child neurodevelopment and anthropometry. As exploratory outcomes, we will also investigate the effect of the sewerage intervention on the reduction of risk of arbovirus infectious diseases.

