##### Rats survey

Rat abundance will be examined at each cluster using tracking boards to quantify the level of rat activity, before and after the interventions. The use of tracking boards to quantify rat presence and activity (as rat abundance proxy) will be performed, following previously described, validated and optimised methods.^28^ Tracking boards will be distributed in each cluster for 2 days in a row and will be scored daily. The overall level of rat presence for each cluster will be estimated based on the percentage of positive tracking boards and the intensity of marks on each board before and at least 3 months immediately after the sewerage intervention. We will compare the abundance and activity of rodents with the environmental leptospiral load in the area.

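### As worded, rat abundance sits in the model that compares soil load between arms; if the post-intervention value enters, the arm coefficient omits any effect acting through rats

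*Protocol article*

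**What the plan says.** In the protocol article, the second paragraph of Statistical analysis sets the soil-load task: "we will conduct environmental analyses of *Leptospira* load between intervention and control clusters to compare environmental risk". Two outcomes, prevalence and log-transformed concentration, are to be modelled "using generalised linear models with random effects to account for clustering within study units". The paragraph closes by saying that the association of contamination with hypothesised predictors of risk ("rat abundance, human movement and ecological data) will also be explored in the model"). No other soil-load model is described.

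The Research aims and hypotheses section introduces three expected effects with "We further hypothesise that this approach will be effective in reducing". The second and third are rat infestation and soil *Leptospira* load; the list reads "2) rat infestation and (3" at that point.

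The Rats survey section measures rats "using tracking boards to quantify the level of rat activity, before and after the interventions" and adds: "We will compare the abundance and activity of rodents with the environmental leptospiral load in the area".

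For the primary outcome, the first paragraph of Statistical analysis adjusts for baseline exposure and for confounders "which are presumably unrelated to the intervention". The soil-load paragraph carries no such limit.

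**The concern.** The article treats rats as the main source of urban contamination: the Abstract says the bacteria spread mainly in rodent urine, and the Introduction calls rats the main urban reservoir. It also expects sewerage to reduce rats. On its own hypotheses, then, one route from sewerage to cleaner soil runs through fewer rats.

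A model that holds post-intervention rat abundance fixed while comparing arms blocks that route. Its arm coefficient is a direct effect. The hypothesis that the intervention lowers soil load concerns the total effect. If rat reduction is an important mechanism, a weak adjusted coefficient could be misread as sewerage having done little for soil contamination.

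**Working it through.** The article gives no soil-load effect size and no share of the effect acting through rats, so there is no stated figure to reproduce. The check has two parts.

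**The text, set side by side**

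1. Statistical analysis: soil load is compared between arms in random-effects models, and rat abundance is to be explored in the model, in the singular and with no second model named.
2. Research aims and hypotheses: rat infestation is expected to fall because of the intervention.
3. Rats survey: rat activity is measured before and after the intervention, so both a baseline and a post-treatment value will exist. Statistical analysis does not say which one enters.
4. Rats survey, Abstract and Introduction: rats are linked to environmental load.

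It follows that if the post-intervention value enters, the arm coefficient excludes the part of the effect that passes through rats. If only the pre-intervention value enters, it does not.

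**The size, under assumptions**

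Let R be the true load ratio between arms and m the share of the log effect acting through rats. Assume that the direct and rat-mediated parts act in the same direction, that effects are additive on the log scale, and that no unmeasured cause is shared by rats and soil load. Then

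log R(adjusted) = (1 − m) × log R, so R(adjusted) = R^(1 − m).

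With an assumed R = 0.50:

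| m (assumed) | R(adjusted) |
|---|---|
| 0 | 0.50^1 = 0.50 |
| 0.25 | 0.50^0.75 = 0.59 |
| 0.50 | 0.50^0.50 = 0.71 |
| 0.75 | 0.50^0.25 = 0.84 |
| 1 | 0.50^0 = 1.00 |

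A simulation checked the algebra in a design shaped like this one: 8 clusters, one period before and one after, 68 soil samples per cluster and period (the count in the article's section on environmental exposure outcomes), and 400 replicates. A linear difference-in-differences model of log10 load was fitted with and without rat abundance. The assumed total effect was −0.5 log10, a different scenario from the ratio of 0.50 above.

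| Share through rats (assumed) | Without rat abundance | With rat abundance | Share of effect retained |
|---|---|---|---|
| 0 | −0.505 | −0.505 | 1.00 |
| 0.25 | −0.499 | −0.375 | 0.75 |
| 0.50 | −0.497 | −0.250 | 0.50 |
| 0.75 | −0.493 | −0.123 | 0.25 |

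The model without rat abundance recovers the assumed total each time; the model with it keeps only the unmediated share. This confirms the formula but says nothing about the true value of m. The formula applies directly to log concentration and only approximately to the binomial prevalence model.

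**The case against.** The strongest reply is that the text never says the arm effect is adjusted for rats. The sentence is about associations between predictors and contamination, and can be read as an additional, mechanistic step. That reading fits the second specific objective, on mechanisms, and the planned comparison of rodent activity with environmental load. The primary-outcome paragraph shows that the authors know the principle. Limitations and bias also describes an impact estimate as a difference-in-differences of averages with time and location fixed effects, in which rats do not appear. Finally, an article may leave covariate sets for a secondary outcome to the full analysis plan.

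Much of this stands. A reader might infer that the plan has committed itself to adjusting the effect away; the wording does not go that far, because exploring may be a later step and the timing of the rat value is not given. A reader might also infer that human movement is a mediator on the same footing as rats. The article does not support that: it expects less human contact with open sewers and measures movement to quantify participants' exposure, but nowhere says that movement changes soil load.

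What does not fall away is that the article makes a statement here and does not simply stay silent. It names one soil-load model for the arm comparison and puts rat abundance in it. The difference-in-differences is not tied to soil load, and the safeguard stated for the primary outcome is not carried over.

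**Conclusion.** The point holds conditionally. Followed literally, and with the post-intervention rat value used, the soil-load model gives an arm coefficient that leaves out whatever part of the effect acts through rats, and the article names no soil-load model that gives the total effect.

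The shortfall rests wholly on an unknown mediated share. It is nil if none of the effect runs through rats. For an assumed true ratio of 0.50, the adjusted ratio is about 0.71 if half of the log effect does; the 1.00 case needs complete mediation. These figures illustrate the mechanism and are not estimates for this trial.

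The primary outcome is not affected. The wording should still be settled before analysis, because the soil-load comparison is how the article's third hypothesised effect is tested.

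**What to change.** State in the Statistical analysis section that the intervention effect on soil prevalence and concentration is estimated without post-intervention rat abundance. Only pre-intervention values and variables that the intervention cannot change, such as rainfall, should enter as covariates. The difference-in-differences in Limitations and bias could serve for this if it is expressly tied to soil load.

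Report the associations with post-intervention rat abundance, human movement and the other predictors in a separate model labelled as a mechanism analysis. Movement belongs there because it is one of the predictors to be explored, not because it is a shown mediator of soil load.

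The cost is a wording change and one additional model fit. No new data are needed, and the planned mechanistic work is kept.
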